### Semistructured Exit Interview

Upon completion of the intervention at month 6, participants are invited to complete a semistructured exit interview conducted over a phone call and recorded, to gauge expectations, perceived benefits, and suggestions for protocol improvement (see Multimedia Appendix 2 for interview guide).

### Treatment Fidelity

Monitoring fidelity is essential to ensuring the intervention’s internal and external validity. In that context, we have developed a fidelity-monitoring plan (Table 1) to address the five areas of intervention fidelity outlined by the National Institute of Health Behavior Change Consortium: design of study, provider training, delivery of treatment, receipt of treatment, and enactment of treatment. Monitoring fidelity is done by the study coordinator, along with the support of the programmer, who provides periodic reports.

**Table 1 table1:** Overview of fidelity measures and areas addressed.

Data source	Monitoring frequency	Study design	Coach training	Intervention delivery	Intervention receipt	Intervention enactment
Coaching call checklist	Monthly	✓	✓	✓		
Coaching call logs	Monthly	✓		✓		
Content resource bank	Quarterly	✓				
Review of the dashboard and its event log	Weekly	✓		✓		
Review of participant food, physical activity, and medication	Weekly				✓	✓
Team meetings to discuss participant progress and protocol adherence	Biweekly	✓	✓	✓	✓	✓

### Outcomes

We are collecting feasibility, process, clinical, and patient-reported outcomes (PROs) during the intervention, with feasibility outcomes serving as the primary end points. As outlined in Tables 2 and 3, our primary outcomes include key feasibility indicators: recruitment, retention, and adherence to the intervention. Secondary outcomes include other feasibility measures such as process measures (eg, time to recruit, percentage of missing data, and enrollment rate), and selected patient-centered and clinical outcomes. The choice of clinical and patient-reported assessments is based on guidelines from the American Diabetes Association [57]. Specifically, diabetes distress is a key PRO, while HbA_1c_ and weight are the key secondary clinical outcomes. Exploratory outcomes include additional PROs (eg, quality of life, depression, self-efficacy, and acceptability of the intervention) and clinical indicators such as blood pressure and lipid profile. PROs are collected using validated instruments such as the Diabetes Distress Scale, EQ-5D, Patient Health Questionnaire-4, and the Diabetes Empowerment Scale. Intervention acceptability is assessed using the Speech User Interface Service Quality, System Usability Scale, and theoretical framework of acceptability scales, in addition to qualitative exit interviews. PA is measured using step count data. Adherence data, including daily self-monitoring of blood glucose and medication adherence, are collected through the ABMS IVR system.

In addition to recruitment, retention, and adherence-related measures, other feasibility measures include process, resource, and management measures such as attrition rate, coach time, time to recruit participants, and technology delivery-related issues (Table 3).

**Table 2 table2:** GODART^a^ outcome measures.

			Instrument	Mode of collection	Collection timepoint	Outcome type

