Our retention efforts include a combination of strategies to ensure participants remain engaged throughout the study. Participants receive regular reminders and check-in phone calls, and study visits are conducted at LabCorp locations close to their residences to reduce the travel burden. The interventions are delivered remotely, minimizing the need for on-site treatments, and participants receive monetary compensation as part of the participation rewards. Additionally, they provide alternative contact information to ensure consistent communication. All participants receive IVR calls throughout the study as part of the engagement strategy. If any participant stops responding, the research coordinator contacts them directly to address any issues. Participants are contacted per the approved Human Subject Protocol. Up to 3 attempts are made to reach out to each participant via phone call, voicemail, or text to verify whether missed calls were due to technical issues or an intention to withdraw from the study. If a participant fails to respond to three consecutive contact attempts, no further outreach is conducted, and the participant is classified as lost to follow-up and removed from the calling list.

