### Intervention Components

#### Automated Behavioral Monitoring System

All participants receive daily calls through the ABMS using IVR technology for a 24-week period. Each participant selects a preferred call time during their initial orientation session with a health coach. If a call is missed, the system automatically places a reminder call 30 minutes later. Participants who miss both calls can return the call at their convenience to record their data.

Unlike traditional self-monitoring approaches that rely on written logs or mobile apps, the ABMS enables participants to speak naturally during calls—for example, “For breakfast, I had a muffin, a banana, and a cup of coffee” or “Today I walked about 5000 steps.” The system captures and processes this information seamlessly using AI-assisted NLP and nutrition databases. The ABMS is designed to collect daily data on four key self-management behaviors: dietary intake, PA, medication adherence, and fasting blood glucose monitoring (yes or no). Figure 3 outlines the 8-step structure of the ABMS used to support diabetes self-management in this study.

During the daily IVR calls, participants report their PA (eg, pedometer step count and engagement in moderate or vigorous activity), medication adherence (eg, whether medications were taken, taken as prescribed, and at the correct time), fasting blood glucose monitoring (yes or no), and dietary intake (meal-specific foods and beverages, including quantities). Textbox 2 lists the daily monitoring questions delivered by the IVR system, and the full branching logic is detailed in Multimedia Appendix 1.

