**Daily medication adherence**
Did you take your diabetes medications today? If yes, did you take your diabetes medications in the amount prescribed by your doctor? If yes, did you take your diabetes medications at the appropriate time today?

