**Daily blood sugar monitoring**
Did you test your blood sugar in the morning today?

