#### Experimentation Group 2: Adapted Versus Fixed Gamified Reward Levels

Participants in this group are randomized into two arms: fixed-reward levels and adapted gamified reward levels; the total possible amount earned over the period of 24 weeks in each arm is US $100.80. The purpose of the rewards is to conduct daily self-monitoring, not as incentives per se to participate in the study. In the fixed-reward arm, participants receive 60 cents per day for answering daily monitoring calls for 24 weeks, earning up to US $100.80 if they answer daily. In the adapted gamified reward arm, participants’ daily rewards increase weekly, starting at US $0.20 per day in the first week, US $0.25 per day in the second, US $0.30 per day in the third, and US $0.65 per day from the fourth week until the end of the study at 6 months. In this arm, missing one day of monitoring (in the past 7 days) drops the reward value by one level (eg, from US $0.65 to US $0.30), with additional missed days dropping the reward further. Participants can rebuild their reward levels by consistently answering daily calls. Like the fixed award arm, a participant answering the call daily for 24 weeks receives up to US $100.80. This resource management–driven study arm will inform us of the extent to which rewards can enable successful behavior change.

### Postintervention Assessments at Month 6

At month 6, similar to the baseline visit, each participant is asked to visit their nearest LabCorp location to provide a blood sample for HbA_1c_, lipid profile, and biometrics. Participants are also sent a 6-month survey packet either electronically via email using REDCap or via physical mail, depending on the participant’s preference. This packet includes all of the surveys in the baseline packet in addition to: Speech User Interface Service Quality, which evaluates the quality, perceived ease of use, and user satisfaction of speech-based interfaces [54]; System Usability Scale, which measures system usability [55]; and the theoretical framework of acceptability survey [56] which assesses the acceptability of the intervention.

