#### Analytic Strategy for Preliminary Effectiveness Analyses

We will also estimate effect sizes as preliminary effectiveness estimates. All statistical analyses will follow an intent-to-treat approach. In line with a pilot study, we will also report 75% and 85% CI estimates in addition to the traditional 95% CIs to further aid in the statistical interpretation of the findings [65]. We will use linear mixed models to estimate effects by accounting for correlated data and benefit from the maximum likelihood estimation procedure that uses all information in the dataset in the presence of missing outcome data. Our overall approach will be similar to Pellegrini et al [38]. To evaluate the main effect of each component on pre-post differences in outcomes, we will use baseline as the reference cell to determine differences in change across time (ie, 6 months vs baseline) [38]. However, these effects will be statistically modeled as component-by-time interactions, with the 6-month outcome as the primary end point. We will also include two-way interactions between components (eg, Factor 1 by Factor 2 by time interaction). We will then identify all the active components or combinations of components, where active is operationalized as a mean reduction of 0.5 units (%) in HbA_1c_ between baseline and month 6 [66,67]. Similar analyses will be done for secondary outcomes. Where information related to minimally clinically important differences is available, we will use it to assess whether the combination is active. For example, an average 5% weight loss is considered to be active in the case of weight. We will leverage the generalized linear modeling framework and resampling-based approaches for nonnormal outcomes. We will conduct exploratory analyses to assess biases in the self-reported PROs. While we are not statistically powered to do mediation or moderation analyses, in line with the MOST Preparatory Phase, we will conduct exploratory mediation and moderator analyses using our tracking data as potential mediators or moderators.

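### Daily medication adherence, glucose testing and steps are seen only on days a call is completed, which the reward factor is meant to change, so reward and mediation results on these exploratory measures need bounds.

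*Protocol article*

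**What the plan says.** Three daily behaviours are listed in Table 2 as exploratory outcomes, with the interactive voice response (IVR) call as their only mode of collection: medication adherence, self-monitoring of blood glucose, and step count. The Outcomes section says: "Adherence data, including daily self-monitoring of blood glucose and medication adherence, are collected through the ABMS IVR system". The section on the Automated Behavioral Monitoring System says the same of activity: "During the daily IVR calls, participants report their PA (eg, pedometer step count and engagement in moderate or vigorous activity), medication adherence". No pedometer upload, glucometer download, pill count or refill record is described.

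The call asks about the same day, for example "Did you take your diabetes medications today" and "Did you test your blood sugar in the morning today". A missed call is followed by one automatic reminder after 30 minutes, and the participant may then phone back. A participant who cannot be reached after three attempts is "classified as lost to follow-up and removed from the calling list".

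On the reward factor, the protocol says: "The purpose of the rewards is to conduct daily self-monitoring". The fixed arm pays US $0.60 per answered day. The adaptive arm moves to a lower reward level when days are missed.

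On missing outcomes, the effectiveness section relies on a "maximum likelihood estimation procedure that uses all information in the dataset in the presence of missing outcome data". Sample Size Justification also allows multiple imputation. The effectiveness section then plans exploratory mediation and moderation "using our tracking data as potential mediators or moderators".

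**The concern.** The randomised reward factor acts on whether the outcome is seen at all. If participants tend to skip the call on days when they also skip medication, testing or walking, the observed days are a favourable selection, and how favourable may differ between reward arms. Randomisation protects a comparison over all days. It does not protect one over the days that happen to be observed.

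Maximum likelihood and multiple imputation, as ordinarily applied, can allow for observation that depends on arm and on a participant's other recorded days. They cannot allow for observation that depends on what happened on the unrecorded day itself. Calls start only after randomisation and orientation, so there is also no pre-randomisation IVR value to condition on.

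At stake is whether a difference in reporting is read as a difference in behaviour. The protocol says the reward comparison should show how far rewards can bring about behaviour change, and the study is meant to inform a later optimisation trial. Mediation through the tracking data would carry the same selection.

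**Working it through.** **Inputs from the protocol.** 24 weeks x 7 = 168 possible call days. The maximum reward is the same in both arms:
- Fixed: 168 x 0.60 = US $100.80.
- Adaptive: 7 x (0.20 + 0.25 + 0.30) + 147 x 0.65 = 5.25 + 95.55 = US $100.80.

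Both totals match the stated figure. The arms therefore differ in how missed days are penalised and in timing, not in the amount for full participation. The protocol gives no answering rate and no adherence rate, so every rate below is an assumption.

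**Formulas.** Let p be the true share of adherent days, and let a1 and a0 be the chances that an adherent or a non-adherent day is observed (call answered or returned).
- Share observed: A = p x a1 + (1 - p) x a0
- Observed-day adherence: o = p x a1 / A
- Documented adherent days out of all days: A x o = p x a1
- Bounds for all-day adherence: from A x o to A x o + (1 - A)

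**Illustration 1: no true difference, p = 70% in both arms.** Assume a1/a0 = 0.80/0.50 (fixed) and 0.90/0.80 (adaptive).

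| | Fixed | Adaptive | Difference (adaptive minus fixed) |
|---|---|---|---|
| Share observed | 0.56 + 0.15 = 71% | 0.63 + 0.24 = 87% | +16 |
| Observed-day adherence | 0.56/0.71 = 78.9% | 0.63/0.87 = 72.4% | -6.5 |
| Documented days | 56% | 63% | +7 |
| Bounds | 56% to 85% | 63% to 76% | -22 to +20 |

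The true difference is zero. The two single-number summaries miss it in opposite directions, while the bounds contain it (63 - 85 = -22; 76 - 56 = +20).

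**Other assumptions tried.** With p from 60% to 80%, and the adaptive arm always assumed to answer more, the error in the observed-day difference ran from 0 to -8.5 points. The error in the documented-day difference ran from +6 to +16 points. The observed-day error is exactly zero when answering does not depend on that day's behaviour: with a1 = a0 = 0.70 in one arm and 0.90 in the other, both arms show the true rate. If the fixed arm were the one answering more, the signs would reverse.

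**Illustration 2: a true difference.** Assume adherence is 85% on observed and 50% on unobserved days in both arms, with 90% and 70% of days observed.
- All days: 0.90 x 0.85 + 0.10 x 0.50 = 81.5%, and 0.70 x 0.85 + 0.30 x 0.50 = 74.5%. Difference +7.
- Observed days: 85% and 85%. Difference 0, an error of -7.
- Documented days: 0.90 x 0.85 = 76.5%, and 0.70 x 0.85 = 59.5%. Difference +17, an error of +10.
- Bounds: 76.5% to 86.5%, and 59.5% to 89.5%. Range for the difference: 76.5 - 89.5 = -13 to 86.5 - 59.5 = +27.

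The bounds need no assumption about unobserved days. Their width within an arm is the share of days unobserved: 10 and 30 points here.

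**The case against.** The strongest reply is that little rests on this. The primary outcomes are feasibility measures, and one of them, the number of monitoring calls answered, is known for everyone. HbA1c, weight and diabetes distress come from a laboratory visit or a survey. The three daily measures are exploratory, mediation is already described as exploratory and unpowered, and percent missing data is itself reported. All of this stands, and it limits the scope. A reader might infer that reward comparisons in general rest on selected days; the documents do not support that.

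A second reply is that no answered-day analysis is written down. The mixed model is described for pre-post change and extended to secondary outcomes, non-normal outcomes go to generalized linear models and resampling, and denominators for daily measures may sit in an analysis plan not shown. It is true that no reward model is spelled out for these outcomes. However, the mediation and moderation use is explicit, and the dependence of measurement on answering is fixed by the design. The limitations mention self-report, recall and underreporting within calls, but not days with no call.

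A third reply is that reminder calls and call-backs recover missed days. They do reduce the gap, but phoning back is still the participant's choice.

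Two stronger readings are tempting. One is that the arm that answers more will look worse because poorer days come into view. That is one possibility; with no rates in the protocol, neither sign nor size can be known. The other is that unanswered days should simply count as non-adherent. Both illustrations show that this can mislead more than the observed-day figure: +7 against -6.5 points in the first, +10 against -7 in the second. As the only mediator, it would build the reward's effect on answering into the mediator.

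**Conclusion.** The concern holds within limits. For medication adherence, glucose testing and steps, and for mediation or moderation using tracking data, observation depends on completing a call, which the reward factor is designed to influence. The stated missing-data methods correct this only under missingness at random given the observed data, which the recorded calls cannot verify. Bias arises if observation depends on that day's behaviour and either that dependence or the answering rate differs between arms. Under the assumed rates, errors of several percentage points in either direction are possible, as is no error at all. The primary feasibility results, HbA1c, weight and the survey outcomes are not affected in this way. It is worth correcting before these exploratory results are reported, but it is not a threat to the study's main conclusions.

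**What to change.** The protocol reports follow-up complete and analysis pending, so the change is to analysis and reporting.

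1. For the reward contrast on each daily yes/no outcome, report by arm: the share of the 168 days with data (returned calls included, days after removal from the calling list counted as unobserved); the observed-day proportion; and the two bounds with all unobserved days counted as adherent or as non-adherent. Give the implied range for the arm difference, pairing one arm's lower bound with the other's upper.
2. Documented adherent days out of 168 may be shown as the lower bound, labelled as documented adherence, meaning reporting and behaviour combined. It should be neither the lead estimate nor the sole mediator.
3. Run mediation with both the observed-day and the documented-day versions, and draw no conclusion about a behavioural pathway unless they agree.
4. Report steps as observed-day means beside the answering rate by arm, and do not read a reward difference in them as behaviour change.
5. Add unobserved call days to the limitations.

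The cost is a few derived variables and one extra table from data already stored. The drawback is that the bounds will be wide if answering is low, which is then an honest statement of what these data can show.

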**Feasibility**						
	Recruitment, retention, completion, and adherence		See Table 3 for more details	Study logs	Ongoing	Primary
**Clinical**						
	**Blood sample**					
		HbA_1c_^b^	Fasting blood draw	Laboratory visit	Baseline and month 6	Secondary
		Lipid profile	Fasting blood draw	Laboratory visit	Baseline and month 6	Exploratory
	**Biometric**					
		Height (in)	Stadiometer	Laboratory visit	Baseline and month 6	Secondary
		Weight (lb)	Weight scale	Laboratory visit	Baseline and month 6	Secondary
		Waist circumference (in)	Measuring tape	Laboratory visit	Baseline and month 6	Secondary
		Blood pressure (mm Hg).	Sphygmomanometer	Laboratory visit	Baseline and month 6	Secondary
**Patient-reported**						
	Distress related to diabetes		Diabetes Distress Scale	Survey	Baseline and month 6	Secondary
	Diabetes management self-efficacy		Diabetes Empowerment Scale	Survey	Baseline and month 6	Exploratory
	Medication adherence		Amount or frequency as prescribed	IVR^c^	Daily	Exploratory
	Self-monitoring of blood glucose		Measured or not	IVR	Daily	Exploratory
	Anxiety and depression		Patient Health Questionnaire-4	Survey	Baseline and month 6	Exploratory
	Health-related quality of life		EQ-5D-5L	Survey	Baseline and month 6	Exploratory
	Step count		Pedometer	IVR	Daily	Exploratory
	Quality, perceived ease of use, and user satisfaction of speech-based interfaces		Speech User Interface Service Quality	Survey	Month 6	Exploratory
	System usability		System Usability Scale	Survey	Month 6	Exploratory
	Acceptability of the intervention		Theoretical framework of acceptability	Survey	Month 6	Exploratory

^a^GODART: Gamified Optimized Diabetes Management with Artificial Intelligence-Powered Rural Telehealth.

^b^HbA_1c_: hemoglobin A_1c_.

^c^IVR: interactive voice response.

**Table 3 table3:** Feasibility outcomes.

Metric and outcome		Outcome variable computation method
**Process**		
	Time taken to recruit	Time from study activation to enrollment of the last participant
	Recruitment rate	Number of participants enrolled per recruitment time period
	Retention rate	Percent of participants completing the trial
	Enrollment rate	Enrolled of eligible or approached
	Decline rate	Percent of eligible individuals who declined participation
	Completion rate	Percent of enrolled participants who completed the study
	Protocol adherence	Total number of sessions attended of the total 24 coaching sessions; number of monitoring calls answered
	Challenges in collecting blood samples using LabCorp	Qualitative data from patients
	Time to complete data collection	Time to complete pre- and postdata collection
	Duration of human coaching	Time to schedule and conduct orientation and diabetes education
	Data entry errors	Data entry errors
	Percent missing data	Percent missing data
**Resource**		
	Patients’ technical difficulties with technology	Number of issues experienced by participants in technology, glucometer, and LabCorp visits
	Number of replacement glucometers requested	Total cost and number of items purchased
	Number of participant contacts by the team required to complete survey data	Number of contacts
**Management**		
	Fidelity across conditions	Number of deviations from protocol per week of technical issues in interactive voice response
	Fidelity across conditions	Frequency, duration, and nonbusiness hour times requested of contact or support

